#### NF training method

2.5.2

The intervention group will perform the NF sensorimotor rhythm (SMR) training protocol, whereas the control group will have EEG measured for the 30 minutes of acupuncture treatment.

The ProComp 2 Neurofeedback system (Promp Infiniti 8 channel system, Model NO. BA500, Thought Technology Ltd., Quebec, Canada) will be used in this trial. After cleaning the electrode location with an abrasive conductive gel (Nuprep, Weaver and company, CO) and filling the electrode cups with conductive gel (ten 20 conductive paste, Weaver and Company, CO), an electrode will be placed at the subject's central scalp area according to the international 10/20 system. A reference and ground electrode will be placed on the left and right earlobes, respectively. A 3-electrode location input impedance will be maintained under 5 kΩ.^[26]^

The training session will consist of a 6-minute baseline trial and a 30-minute NF training trial, divided into 6 segments. To determine threshold values, each subject will be measured at baseline SMR wave (12–15 Hz, low beta waves) for 3 minutes with eyes closed and 3 minutes with eyes open. NF training, which is designed to increase threshold SMR values, will be performed 6 times for 5 minutes with 20 to 30 seconds of rest between each trial. BPM and HRV values will also be collected in each trial. The threshold value at each trial is newly set according to the subject's feedback.

### Sample size

2.6

Considering a 10% dropout rate, we conclude that a total of 44 patients is needed to measure the feasibility of combined NF-acupuncture treatment (effect size 0.8, 0.05 significance level in 2-tailed test, 69% power).^[27]^ If the dropout rate is higher than expected, even after deliberation, the number of participants can be adjusted.

### Randomization, blinding

2.7

The investigator in charge of randomization, who will not be involved in the trial, will generate the random sequence list using SAS Version 9.4 (SAS Institute. Inc., Cary, NC) program, and each randomized code will be kept in sealed envelopes, to be managed by the PI. For randomized allocation, the stratified block randomization method will be used, for which the stratification factors will be gender and age. This method involves stratification into 4 subgroups, by age and gender: 1 group of 50 to 60 years old individuals and 1 of 61 to 75 years old individuals for each gender. The investigator assigning the randomization code will open the sealed envelope in front of the participants to whom the identification code is assigned. This investigator will record the date of opening, sign the envelope, and store it separately.

In this trial, blinding of the subjects is not possible; assessor blinding will therefore be performed to control for bias. An investigator doctor not involved in randomization will perform acupuncture on subjects before NF training or simple EEG, will be blinded to the type of treatment to be administered, and will subsequently perform an evaluation of the effectiveness and safety.

Blinding breaking should be determined on a case-by-case basis and considered only in serious medical emergencies. If the investigator determines that blinding breaking is necessary, they can contact the PI or sponsor to obtain consent, and subsequently document the breaking procedure.

### Statistical analysis

2.8

All categorical data will be presented as frequencies or percentiles, and will be analyzed by the Pearson chi-squared test or Fisher exact test. All numeric data will be presented as mean, standard deviation, and will be analyzed by Student independent sample *t* test or Wilcoxon rank-sum test to determine normality. Efficacy analysis will be conducted according to the primary full analysis set principle and secondarily by the per protocol principle. All statistical analyses will be based on a two-tailed test and statistically, the significance is set at *P* < .05. The analysis tool will be SAS Version 9.4 (SAS Institute. Inc., Cary, NC). Missing values will be imputed by the last-observation-carried-forward method.

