### Study procedure

2.4

All consenting participants will be subjected to the measurement of vital signs (blood pressure, pulse rate, body temperature), demographic information survey, medical history (past, present, family), physical examination, laboratory tests, and electrocardiogram tests. Eligible participants who meet the inclusion and exclusion criteria will receive a schedule of visits (screening).

At visit 1, the investigator will check the subject's vital signs and test ADAS-cog, K-BDI, BAQ, DMTS (response and accuracy), and fNIRS (Oxy-Hb, deOxy-Hb). The control group will receive acupuncture treatment for 30 minutes, while measuring a simple EEG with NF, and the intervention group will receive acupuncture for a minute while performing the NF training protocol (5 times for 5 minutes, 30–60 seconds of rest between each trial). In the meantime, the investigator will check the subject's BPM and HRV. The investigator will check the subject's adverse reactions and concomitant medications and inform them that cigarettes and caffeine must be avoided 2 hours before the test, as they affect the HRV. From visits 2 to 24, both groups will be treated in the same manner as visit 1, and BPM HRV will be checked in the meantime. The investigator will check the subject's adverse reactions and concomitant medications and inform them in the same manner as on visit 1. At visit 24, the investigator will check the subject's vital signs and test ADAS-cog, K-BDI, BAQ, DMTS (response and accuracy), and fNIRS (Oxy-Hb, deOxy-Hb). Additional visits may be performed at any time if deemed necessary by the investigator's judgment, or following the subject's request. In the event of an unexpected visit, the following tests will be performed: vital signs, checking adverse reactions or concomitant drugs, and laboratory tests. In principle, administration of concomitant drugs will be prohibited during the trial, and when combination therapy may occur, it will be decided whether or not to drop out or exclude at the discretion of the principle investigator (PI). A detailed outline of the schedules is shown in Table 1.

**Table 1 T1:** Schedule of trial visits.

	Study period				
Visit	Screening	1	2 to 24	25	UV
Informed consent	О				
Eligibility screen	О				
Demographic information	О				
Drug history	О				
Medical history	О				
Vital signs	О	О	О	О	О
Laboratory test	О				Δ
EKG	О				Δ
MoCA-K	О			О	
ADAS-cog		О		О	
K-BDI		О		О	
BAQ		О		О	
HRV		О	О	О	

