#### Primary outcome

2.9.1

MoCA-K will be the primary outcome. The endpoint will be the change in the MoCA-K score from screening to visit 25. We will use the covariance analysis model that includes each group as a fixed factor, MoCA-K score as a dependent variable, and the difference in demographic characteristics as a covariate.

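### With MoCA-K measured only at screening and visit 25, LOCF gives any full-analysis-set participant without a visit 25 score a change of exactly zero

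*Protocol article*

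**What the plan says.** Section 2.8 (Statistical analysis) gives one rule for missing data, with no exception by outcome: "Missing values will be imputed by the last-observation-carried-forward method". The same section sets the analysis populations: "Efficacy analysis will be conducted according to the primary full analysis set principle and secondarily by the per protocol principle". The article does not define the full analysis set.

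Section 2.9.1 (Primary outcome) defines the endpoint: "The endpoint will be the change in the MoCA-K score from screening to visit 25". The model is an analysis of covariance: "We will use the covariance analysis model that includes each group as a fixed factor, MoCA-K score as a dependent variable", with demographic differences as covariate.

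Table 1 marks MoCA-K at screening and at visit 25 and nowhere else. The text of section 2.4 (Study procedure) agrees. MoCA-K is not listed among the visit 1 tests. For the end of treatment the text says: "At visit 24, the investigator will check the subject's vital signs and test ADAS-cog, K-BDI, BAQ, DMTS (response and accuracy), and fNIRS (Oxy-Hb, deOxy-Hb"; MoCA-K is again absent. At unscheduled visits, "the following tests will be performed: vital signs, checking adverse reactions or concomitant drugs, and laboratory tests". The article describes no MoCA-K at early withdrawal.

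Section 2.6 (Sample size) plans 44 patients: "Considering a 10% dropout rate", with "effect size 0.8, 0.05 significance level in 2-tailed test, 69% power".

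**The concern.** LOCF is usually understood to carry the last on-treatment value. Here no on-treatment MoCA-K exists, so the rule carries the pre-treatment value, and what is called LOCF is baseline carried forward. If the dependent variable is read as the visit 25 score and not the change, the imputed score equals the screening score and the implied change is still zero.

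Zero is not a neutral value. Both arms receive active treatment. Entry requires a MoCA-K of 22 or less, and that same screening score serves as baseline, so some upward shift at retest is to be expected in both arms through regression to the mean. The rule denies that shift only to participants without a visit 25 score.

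Three things follow for the primary analysis:

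- With equal dropout, the treatment difference is diluted.
- With unequal dropout, a difference in attendance becomes a difference in outcome. Participants know their treatment (section 2.7), so unequal dropout is possible, though nothing in the article shows that it will occur.
- The imputed zeros enter the standard error as if they were measured.

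**Working it through.** **Inputs from the article.** Effect 0.8 SD, two-sided 0.05, stated power 69%, dropout 10% (section 2.6); 22 per arm (abstract).

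**Assumptions, not in the article.** Change scores have SD 1 in each arm among those observed. Mean control-arm change m is 0 to 1.0 SD, and the mean combined-arm change is m + 0.8. Dropout means no visit 25 MoCA-K and is unrelated to outcome. The calculation uses a two-sample t test on change, not the full covariance model.

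**Step 1: the plan's own figure.** With 20 completers per arm, the noncentrality is 0.8 / √(2/20) = 2.53 on 38 degrees of freedom, and power is 69.3%. The stated 69% reproduces, and 20 × 1.1 = 22 per arm gives 44. The 69% is therefore a completer figure; it does not allow for imputed zeros.

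**Step 2: what the rule does.** If a proportion p of an arm with mean change μ is set to zero:

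- mean = (1 − p) μ
- variance = (1 − p) + p(1 − p) μ²

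Power then comes from the noncentral t with 22 per arm.

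**Step 3: 10% dropout in both arms.** The difference is 0.9 × (m + 0.8) − 0.9 × m = 0.72 SD for any m.

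| m | variance, control | variance, combined | noncentrality | power |
|---|---|---|---|---|
| 0 | 0.900 | 0.958 | 2.48 | 68% |
| 1.0 | 0.990 | 1.192 | 2.29 | 61% |

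A simulation with exactly 2 dropouts per arm gives much the same: 0.8 × 20/22 = 0.727 SD, and power of 69% (m = 0) to 63% (m = 1.0).

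**Step 4: unequal dropout, assumed 5% v 20%.**

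- Combined arm loses more: 0.80 × (m + 0.8) − 0.95 × m = 0.64 − 0.15m. This gives 0.64 SD (power 58%) at m = 0 and 0.49 SD (power 31%) at m = 1.0.
- Control arm loses more: 0.95 × (m + 0.8) − 0.80 × m = 0.76 + 0.15m. This gives 0.76 SD at m = 0 and 0.91 SD at m = 1.0. The true 0.8 SD is exceeded once m is above 0.04/0.15 = 0.27 SD.

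**Step 5: no true difference, common gain g.** The same split gives a false difference of (0.95 − 0.80) × g = 0.15g, against the arm that loses more. That is 0.075 SD at g = 0.5 and 0.15 SD at g = 1.0.

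**The case against.** **Not every dropout is affected.** A reader might infer that everyone who discontinues is scored as unchanged. The article does not support that: someone who stops sessions but attends visit 25 keeps an observed score. The point also depends on the full analysis set. If the full protocol requires a post-baseline MoCA-K, LOCF has nothing to impute for the primary outcome. The text shown does not say so, and in that case the rule would be empty for this endpoint.

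**Nor are all outcomes affected.** It is tempting to extend the argument to ADAS-cog, K-BDI, BAQ, DMTS and fNIRS. Section 2.4 places these at visit 24, while Table 1 and section 2.9.2 place them at visit 25. If both assessments take place, a visit 24 value could be carried. HRV and BPM have interim values. This objection stands, and the point is limited to MoCA-K.

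**The planned dropout does little harm.** This also stands. Ten per cent of 44 is about 4 patients, and with no control-arm gain the loss is about 1 power point. The 8-point loss needs an assumed 1.0 SD gain.

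**The unequal-dropout figures are scenarios.** A 5% v 20% split averages 12.5%, above the planned rate, and both arms attend the same 24 visits. The range for m covers improvement only. With a 0.5 SD control decline and the combined arm losing more, the difference is 0.64 + 0.075 = 0.715 SD and power is about 69%. The figures show how far the rule can move the result; they do not predict that it will.

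**It is a pilot, and an analysis plan may follow.** Sections 2.1 and 2.8 nevertheless set an efficacy objective tested at the 5% level, and the imputation rule is stated, not left open.

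**Conclusion.** The point holds for the primary outcome. For a participant retained in the full analysis set without a visit 25 MoCA-K, the stated rule fixes the change at zero and treats it as data.

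At the plan's own dropout rate, equal between arms, the cost is a 10% attenuation (0.80 to 0.72 SD) and power of about 61-68% against 69.3%. A reader might infer that power collapses, or that the rule is at least conservative. Neither follows. The low power figures need an assumed dropout imbalance and an assumed control-arm gain, and the opposite imbalance can inflate the effect, up to 0.91 SD in the range examined. The reason to act is that the direction of the bias depends on which arm loses more patients, which cannot be known in advance.

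All sizes rest on the assumed control-arm change, dropout unrelated to outcome, and a t test on change. Severity: should-fix.

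**What to change.** In section 2.8, replace LOCF as the primary rule for MoCA-K with an analysis valid under missing at random. Two forms would serve:

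- analysis of covariance on observed visit 25 MoCA-K scores, with screening MoCA-K as a covariate; or
- multiple imputation of the visit 25 score from arm and screening MoCA-K.

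With a single follow-up the two should give very similar answers, so the simpler one is enough. Keep the present rule only as a sensitivity analysis, and label it baseline carried forward.

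The cost is an amended sentence, with the ethics approval that section 2.12 requires for protocol revisions, and a little more programming. If observed data are used, slightly fewer patients are analysed: about 20 per arm at 10% dropout, which is the number on which the stated 69% power already rests. No extra patients or assessments are needed.

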### Efficacy assessment

2.9

#### Primary outcome

2.9.1

MoCA-K will be the primary outcome. The endpoint will be the change in the MoCA-K score from screening to visit 25. We will use the covariance analysis model that includes each group as a fixed factor, MoCA-K score as a dependent variable, and the difference in demographic characteristics as a covariate.

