##### Inclusion criteria

2.3.2.1

1.Males and females aged between 50 and 75 years.2.Participants diagnosed with MND based on the diagnostic and statistical manual of mental disorders-5 diagnostic criteria.3.Participants with MoCA-K score of 22 or less.4.Participants who have a level of education of more than 6 years (more than elementary education level).5.Participants or authorized surrogates who voluntarily sign the clinical trial consent form.

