#### Secondary outcomes

2.9.2

ADAS-cog, K-BDI, BAQ, fNIRS, DMTS, BPM, and HRV will be the secondary outcomes. Endpoints will include the change in ADAS-cog, K-BDI, BAQ, DMTS scores, and fNIRS values from visit 1 to visit 25; HRV values from visit 1 to visit 5, 9, 13, 21, and 25; and BMP values from visit 1 to visit 25. As primary outcome, we will use the covariance analysis model that includes each group as a fixed factor, ADAS-cog, K-BDI, BAQ, DMTS scores and HRV, BPM, and fNIRS values as dependent variables, and differences in demographic characteristics as covariates. A paired *t* test or Wilcoxon signed-rank test will be performed on the same participant on the secondary outcome before and after treatment in each group.

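### The primary ANCOVA names the MoCA-K score, not its change, as dependent variable and omits the screening value, which leaves the estimate ambiguous and less precise than it could be

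*Protocol article*

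**What the plan says.** Section 2.9.1 fixes the endpoint first: "The endpoint will be the change in the MoCA-K score from screening to visit 25". The next sentence gives the model: "We will use the covariance analysis model that includes each group as a fixed factor, MoCA-K score as a dependent variable". The only adjustment it goes on to name is demographic: "and the difference in demographic characteristics as a covariate". It does not say at which time point the score is taken, and it does not name the screening value as a covariate. Section 2.9.2 carries the same design over to the secondary outcomes: "we will use the covariance analysis model that includes each group as a fixed factor". The secondary measures take the place of MoCA-K there, and the adjustment is again demographic only: "and differences in demographic characteristics as covariates". Section 2.8 adds no baseline term.

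The baseline values are available. Section 2.3.2.1 makes the screening score an entry condition ("Participants with MoCA-K score of 22 or less"), and Table 1 schedules MoCA-K at screening and at visit 25. ADAS-cog, K-BDI, BAQ, the matching task and fNIRS are scheduled at visits 1 and 25. Table 1 lists demographic information and MoCA-K as separate items, so the demographic covariates cannot be taken to include the screening score.

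Section 2.6 sets the size at 44 patients with an allowance for loss ("Considering a 10% dropout rate") and states its other assumptions in brackets: "effect size 0.8, 0.05 significance level in 2-tailed test, 69% power".

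**The concern.** Two sentences in 2.9.1 point to different dependent variables, a change and a score, and the model lacks the one term that would make the choice immaterial. Without the screening value as a covariate, the two readings are different analyses with different estimates, standard errors and p-values. With it, they give the same treatment effect.

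Two things are at stake. First, the primary result is not fully determined by the text, in a trial whose stated objective is to evaluate efficacy and which tests at a two-sided 5% level. Secondly, with about 20 analysed patients per arm, a chance difference in screening MoCA-K carries partly into the estimate, and precision is given up in a design that states only 69% power. Stratification is by age and gender, which does not directly balance screening MoCA-K.

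**Working it through.** **Inputs from the protocol article.** Effect size 0.8, two-sided 0.05, 69% power, 10% dropout, 44 patients in two equal groups (2.2, 2.6). **Assumed, because not given:** the correlation ρ between screening and visit 25 MoCA-K, taken as 0.3, 0.5 and 0.7; equal SDs at both times; no other covariates. The article does not say whether 0.8 is in SDs of the score or of the change, so both are shown.

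**1. The plan's own figure.** For a two-sample t test with 20 per arm, the noncentrality is 0.8 × √(20/2) = 2.53 on 38 degrees of freedom, and the power is 69.3%. Dropout taken as 20 × 1.10 = 22 per arm gives 44. The stated figures reproduce, and they use no baseline adjustment.

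**2. Why the two readings differ.** Let D be the between-arm difference in mean screening score. The score estimate minus the change estimate equals D exactly when there are no other covariates. Given D, the score estimate is shifted by about ρD and the change estimate by about ρD − D = −(1−ρ)D. With 20 per arm, D has a standard error of √(2/20) = 0.32 baseline SDs. An imbalance of that size shifts the score estimate by 0.09, 0.16 or 0.22 SD and the change estimate by −0.22, −0.16 or −0.09 SD at ρ = 0.3, 0.5 or 0.7.

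**3. Why they agree once baseline is in the model.** If change = a + τ·arm + β·baseline, then score = a + τ·arm + (β+1)·baseline. The residuals, τ and its standard error are the same. One simulated set of 40 patients confirms this: without baseline, the effect was 1.42 (SE 0.712, p = 0.053) for score and 1.59 (SE 0.517, p = 0.004) for change; with baseline, both gave 1.54 (SE 0.476, p = 0.0025).

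**4. Variances.** Setting the score variance to 1, change has variance 2(1−ρ) and baseline-adjusted ANCOVA has 1−ρ². The ratio of ANCOVA to score is therefore 1−ρ², and of ANCOVA to change (1+ρ)/2.

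| ρ (assumed) | ANCOVA/score | ANCOVA/change | change/score |
|---|---|---|---|
| 0.3 | 0.91 | 0.65 | 1.4 |
| 0.5 | 0.75 | 0.75 | 1.0 |
| 0.7 | 0.51 | 0.85 | 0.6 |

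**5. Power with 20 per arm** (noncentral t; one further degree of freedom lost for ANCOVA). The adjusted effect size is 0.8/√((1+ρ)/2) if 0.8 is in change SDs, and 0.8/√(1−ρ²) if it is in score SDs.

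| Scale of 0.8 | ρ | Change analysed | Score analysed | With screening value |
|---|---|---|---|---|
| change SDs | 0.3 | 69% | 83% | 86% |
| change SDs | 0.5 | 69% | 69% | 81% |
| change SDs | 0.7 | 69% | 48% | 76% |
| score SDs | 0.3 | 55% | 69% | 73% |
| score SDs | 0.5 | 69% | 69% | 81% |
| score SDs | 0.7 | 89% | 69% | 93% |

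The adjusted analysis has the highest power in every row. Which unadjusted analysis comes second depends on ρ, which is unknown.

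**The case against.** The strongest reply is that the endpoint sentence governs the model sentence. Read in order, the dependent variable is loose shorthand for the change just defined, and the screening score then enters by subtraction. That is the more natural reading, and on it the gain from adjustment shrinks as ρ rises: 76% against 69% at ρ = 0.7. This part stands. It means a reader who infers that the plan throws the baseline away is right only if the raw score is analysed.

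A second reply is that this is a pilot, openly planned at 69% power, and that randomisation keeps either analysis unbiased on average with valid type I error. That also stands. A reader might infer that the planned analysis is biased or invalid, and the text does not support that.

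Three further inferences go too far. An imbalance does not pass fully into the score estimate; it passes in proportion to ρ. The documents give no figure showing that screening MoCA-K is the most prognostic variable, and the entry limit of 22 narrows its range and may lower ρ. The two sets of power gains rest on different scales for the 0.8 and should not be merged into one range of benefit.

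It does not stand that the matter is simply left to an unseen analysis plan. The article states the factor, the dependent variable and the covariates, and what it states omits the baseline value.

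**Conclusion.** The point holds as a matter of efficiency and clarity. Section 2.9.1 names a change as endpoint and a score as dependent variable, and the stated covariates in 2.9.1 and 2.9.2 leave out a baseline value that is already collected. The cost is an ambiguous primary analysis, exposure to chance imbalance of ρD or −(1−ρ)D, and lost precision. With 20 per arm and an effect size of 0.8, adjustment would raise power from 69% to 86%, 81% or 76% (change analysed, change SDs), or to 73%, 81% or 93% (score analysed, score SDs), at ρ = 0.3, 0.5 or 0.7. These figures are illustrations: ρ is assumed, and so are equal SDs at both times. The omission of baseline and the mismatch between endpoint and dependent variable do not depend on those assumptions. The change should be made because it is close to free, not because the planned comparison would be invalid.

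**What to change.** In 2.9.1, name one dependent variable, either MoCA-K at visit 25 or its change from screening, and include screening MoCA-K as a mandatory covariate alongside treatment group. For a fixed set of other covariates the treatment effect is then identical under either choice, so that set should be named in advance too. In 2.9.2, include each outcome's own visit 1 value in the same way. One check is needed there: section 2.4 has heart rate variability and breathing rate recorded during the treatment session, so for those two the visit 1 value is a true baseline only if it is taken before that session's treatment begins.

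The cost is about one sentence in each section and one degree of freedom per model. No new data are needed for the primary outcome or for the secondary outcomes tested at visit 1. The change should be recorded before outcome data are seen by arm.

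### The ANCOVA covariates appear to depend on which demographics differ between arms, and gender, age group and screening MoCA-K are not fixed in the model; the likely cost is power, not a false positive

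*Protocol article*

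**What the plan says.** Section 2.9.1 defines the primary endpoint: "The endpoint will be the change in the MoCA-K score from screening to visit 25". It then gives the model: "We will use the covariance analysis model that includes each group as a fixed factor, MoCA-K score as a dependent variable", with "the difference in demographic characteristics as a covariate". Section 2.9.2 uses the same model for all secondary outcomes, with "differences in demographic characteristics as covariates".

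Neither section names a covariate or says what counts as a difference. Section 2.7 states that "the stratification factors will be gender and age" and forms four strata: "1 group of 50 to 60 years old individuals and 1 of 61 to 75 years old individuals for each gender". Sections 2.8 and 2.9 do not say that these factors enter the analysis, and they do not name the screening MoCA-K score as a covariate.

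**The concern.** Read naturally, the covariate rule looks at the randomised groups first and adjusts for whatever demographics differ. That has three drawbacks.

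- The primary model is not settled until the data are in.
- Chance imbalance is a poor guide to what predicts outcome. A balanced but prognostic variable is left out, and an imbalanced but irrelevant one goes in.
- Gender and age group are the demographics least likely to differ, because stratified blocks balance them. The rule therefore tends to omit the two factors that the design singled out.

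When randomisation is balanced on a prognostic factor and the analysis ignores it, the treatment estimate is more precise than its standard error says. The test rejects too rarely. Section 2.6 plans for only 69% power, so avoidable loss matters here.

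**Working it through.** **The plan's own figure.** Section 2.6 gives "effect size 0.8, 0.05 significance level in 2-tailed test, 69% power", with 44 randomised and 10% dropout. 44 × 0.9 = 39.6, so about 40 patients, 20 per arm. The non-centrality is 0.8 × √(20/2) = 2.530 and the two-sided 5% critical value on 38 degrees of freedom is 2.024. The power from the noncentral t distribution is 69.3%. The stated 69% reproduces and corresponds to an unadjusted comparison.

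**Effect of ignoring the strata.** Inputs from the article: 20 evaluable per arm, four strata, d = 0.8, two-sided 5%. Assumptions: strata of equal size, exact balance within each, and a share R² of the within-arm outcome variance explained by gender and age group. The article gives no R², so a range from 0 to 0.20 is shown. Scale the outcome variance to 1.

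- True standard error of the difference: √(2(1 − R²)/20).
- Expected pooled variance used by the test that ignores strata: (40R² + 38(1 − R²))/38 = 1 + 2R²/38.
- Rejection bar in units of the true standard error: c = 2.024 × √((1 + 2R²/38)/(1 − R²)).
- Type I error ≈ P(|t₃₈| > c).
- Non-centrality at d = 0.8: 2.530/√(1 − R²). Power ignoring strata uses the bar c. Power with gender and age group in the model uses 40 − 4 = 36 degrees of freedom and a critical value of 2.028.

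| R² | c | Type I error, strata ignored | Non-centrality | Power, strata ignored | Power, strata in model | Gain (points) |
|---|---|---|---|---|---|---|
| 0 | 2.024 | 5.0% | 2.530 | 69.3% | 69.2% | −0.1 |
| 0.05 | 2.080 | 4.4% | 2.596 | 69.7% | 71.4% | 1.7 |
| 0.10 | 2.140 | 3.9% | 2.667 | 70.0% | 73.7% | 3.7 |
| 0.20 | 2.275 | 2.9% | 2.828 | 70.9% | 78.6% | 7.7 |

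Simulation of the same setting agrees: type I error of about 4.9%, 4.5%, 3.8% and 2.7% with strata ignored, and power of about 69%, 71%, 74% and 79% with strata in the model.

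**Effect of choosing covariates by imbalance.** A second simulation used 40 patients in stratified blocks of 4. The candidates were gender, age, education and screening MoCA-K, each entering only if it differed at P < .05. Block size, candidates and threshold are assumptions. There were 6,000 runs per setting for type I error and 4,000 for power. Total R² is the share explained by all prognostic variables together.

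| Total R² | Type I error, selected by imbalance | Power, selected | Power, strata plus screening MoCA-K fixed |
|---|---|---|---|
| 0 | 5.2% | 70% | 68% |
| 0.25 | 3.6% | 70% | 77% |
| 0.50 | 2.3% | 71% | 87% |

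The fixed model held its type I error at 4.7 to 5.2%. At least one covariate was selected in only about 10% of runs, so the selecting analysis behaves almost like an unadjusted one. The gains in the last column include the contribution of screening MoCA-K and are not due to the strata alone.

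**The case against.** The strongest reply is that the phrase is loose English and may mean only that demographics are adjusted for. Gender and age would then be in the model. That reading cannot be excluded, so the selection reading is likely but not certain. Even so, the variables are unnamed and the model is still undetermined.

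It can also be said that a journal article leaves the covariate list to the full protocol or SAP. Silence alone would indeed be no finding. The point rests on the rule that is printed, which a later document would have to replace, not merely fill in.

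The size depends on assumed R². With weakly prognostic strata there is little conservatism and little to gain, and the honest range starts at zero. This part of the reply stands.

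Two stronger readings are tempting, and the article does not support them.

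- A reader might infer that the false-positive rate is inflated. Selection by baseline imbalance keeps it at or below about 5%; the 5.2% above is within simulation error. Inflation appears only if the choice is steered by the outcome: taking the most favourable of 16 covariate sets gave 7.3% to 11.5%. The wording does not prevent that, but nothing in the article says it will happen.
- A reader might infer that section 2.8 sets up a rival primary test, since it assigns a t test or a "Wilcoxon rank-sum test to determine normality" to all numeric data. Neither test determines normality, and the phrase is most plausibly a slip for choosing between them according to normality. Sections 2.9.1 and 2.9.2 specifically assign ANCOVA to the efficacy outcomes, and the specific rule governs the general one.

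**Conclusion.** The concern holds in a limited form. The stated rule most naturally makes the primary and secondary models depend on observed imbalance. It does not commit the stratification factors or the screening score to the model. The treatment comparison stays valid through randomisation, and the expected consequence is a conservative test with less power than the same patients could give. For the strata alone, type I error falls from about 5% to just under 3%, and about 0 to 8 points of power at d = 0.8 are forgone, as strata R² goes from 0 to 20%. Those R² values are assumptions, as are equal strata and exact balance. This is worth correcting because the remedy is nearly free.

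**What to change.** In 2.9.1, replace the covariate phrase with a fixed list: gender, age group (50–60 / 61–75) and screening MoCA-K, included whatever imbalance is observed. State that this ANCOVA is the primary between-group test. With screening MoCA-K in the model, the estimated group difference is the same whether the dependent variable is the visit 25 score or the change. That also removes any doubt left by naming the change as endpoint and the score as dependent variable.

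In 2.9.2, use gender, age group and each outcome's own visit 1 value; screening MoCA-K is not the baseline of those outcomes. Section 2.4 has HRV and BPM checked during the visit 1 session, so the text should say which reading serves as their baseline.

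The cost is wording plus three degrees of freedom: 40 − 2 = 38 residual degrees of freedom become 35. If nothing is prognostic, the simulated loss of power is about 2 points (70% to 68%).
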